**AMENDMENT # 2, January 30, 2007**

RE: Addition of a sub-study titled: A study of novel adipocyte cytokines and the risk of gestational diabetes mellitus

General description: The purpose of this amendment is to change the "Week 16" visit during pregnancy follow-up from a telephone visit to a clinic visit. The new "Week 16" visit will be identical to other pregnancy clinic visits with the same questionnaires administered and same blood and urine samples obtained. Additional text giving the background and rationale for this sub-study is also added to the protocol

This document includes only the sections in the protocol where changes are made.

Modification to section D.8 on page 33: Pregnancy follow-up

**On page 34-35, the 5th and 6th paragraphs of this section were:**

The University of Utah will perform seven visits during pregnancy based around routinely scheduled prenatal clinic visits whenever possible to minimize the burden on participants. When study visits are completed at the participant's physician's office (rather than the research clinic), all typical visit activities will still be performed except not all the information on the Short Physical Measurements Form may be available. The week 8 pregnancy visit needs to occur at the research clinic since new randomized pill bottles will need to be obtained for the participant. This supply of pills should be enough to cover the period until week 36 of pregnancy. In Utah, the approximate times of the visits will be: week 4, 8, 12, 20, 28, 36 and parturition (See Table 1 below for timing of contacts and activities). The last active or passive follow-up visit where the positive pregnancy test was obtained is considered week 4 of pregnancy. Specimen collection will be obtained at the 8, 12, 20 and 28 week visits. If the 12, 20, and 28 week visits are done at the participant's physician's office and routine labs are to be drawn at that visit, every effort will be made to obtain the study labs at the same time. There will be no specimen collection at the 36 week visit. Utah will perform monthly phone calls at weeks 16, 24, and 32 to conduct the safety interview, adherence assessment, and the monthly pregnancy questionnaire. The study ultrasounds will be performed at separate visits at one of the four research clinic sites and will be conducted at 6 ½ weeks to confirm and date the pregnancy. Utah will also collect placenta at the time of miscarriage (when feasible) and after delivery. Cord blood will also be collected at the time of delivery when feasible.

The University at Buffalo will perform five pregnancy visits at weeks 4, 8, 12, 20, and 28. The last active or passive follow-up visit where the positive pregnancy test was obtained is considered week 4 of pregnancy. Specimen collection will be obtained at the 8, 12, 20 and 28 week visits. A study ultrasound will be performed at 6 ½ weeks

[figure not shown]

to confirm and date the pregnancy. In between study visits (at weeks 16, 24, 32, and 36), Buffalo will perform monthly phone calls to conduct the safety interview, adherence assessment, and the monthly pregnancy questionnaire.

**It is changed to:**

The University of Utah will perform **eight** visits during pregnancy based around routinely scheduled prenatal clinic visits whenever possible to minimize the burden on participants. When study visits are completed at the participant's physician's office (rather than the research clinic), all typical visit activities will still be performed except not all the information on the Short Physical Measurements Form may be available. The week 8 pregnancy visit needs to occur at the research clinic since new randomized pill bottles will need to be obtained for the participant. This supply of pills should be enough to cover the period until week 36 of pregnancy. In Utah, the approximate times of the visits will be: week 4, 8, 12, **16**, 20, 28, 36 and parturition (See Table 1 below for timing of contacts and activities). The last active or passive follow-up visit where the positive pregnancy test was obtained is considered week 4 of pregnancy. Specimen collection will be obtained at the 8, 12, **16**, 20 and 28 week visits. If the 12, 20, and 28 week visits are done at the participant's physician's office and routine labs are to be drawn at that visit, every effort will be made to obtain the study labs at the same time. There will be no specimen collection at the 36 week visit. Utah will perform monthly phone calls at weeks **24**, and 32 to conduct the safety interview, adherence assessment, and the monthly pregnancy questionnaire. The study ultrasounds will be performed at separate visits at one of the four research clinic sites and will be conducted at 6 ½ weeks to confirm and date the pregnancy. Utah will also collect placenta at the time of miscarriage (when feasible) and after delivery. Cord blood will also be collected at the time of delivery when feasible.

The University at Buffalo will perform **six** pregnancy visits at weeks 4, 8, 12, **16**, 20, and 28. The last active or passive follow-up visit where the positive pregnancy test was obtained is considered week 4 of pregnancy. Specimen collection will be obtained at the 8, 12, **16**, 20 and 28 week visits. A study ultrasound will be performed at 6 ½ weeks to confirm and date the pregnancy. In between study visits (at weeks **24**, 32, and 36), Buffalo will perform monthly phone calls to conduct the safety interview, adherence assessment, and the monthly pregnancy questionnaire.

Modification to Figure 3 page 36: Timeline for participant follow-up during pregnancy

The change: Week 16 visit was changed from a phone visit (yellow arrow) to a clinic visit (red arrow).

[figure not shown][figure not shown]

\* Day 28 represent the end of cycle visit with a positive pregnancy test

#### Modification to Table 1 page 36. Activities performed during pregnancy follow-up visits

The change: A new column was added for week 16 pregnancy clinic visit

|                                | Pregnancy Visits     |     |   |    |    |        |    |              |             |
|--------------------------------|----------------------|-----|---|----|----|--------|----|--------------|-------------|
|                                | Week gestational age |     |   |    |    |        |    |              |             |
|                                | 4                    | 6.5 | 8 | 12 | 16 | 20     | 28 | 36
(Utah) | Parturition |
| Utah & Buffalo                 |                      |     |   |    |    |        |    |              |             |
| Blood Specimen                 | X                    |     | X | X  | X  | X      | X  |              | X (Utah)    |
| Urine Specimen                 | X                    |     | X | X  | X  | X      | X  |              |             |
| Home Daily Urine Collection    | X                    | →   | X |    |    |        |    |              |             |
| Pregnancy Daily Diaries        | X                    | →   | X |    |    |        |    |              |             |
|                                |                      | X   |   |    |    | X      |    |              |             |
| Study Ultrasound               |                      |     |   |    |    | (Utah) |    |              |             |
| Blood Pressure                 | X                    |     | X | X  | X  | X      | X  | X            |             |
| Anthropometric Measurements    | X                    |     | X | X  | X  | X      | X  | X            |             |
| Pregnancy Questionnaire        |                      |     |   | X  | X  | X      | X  | X            |             |
| Safety Interview               | X                    |     | X | X  | X  | X      | X  | X            |             |
| Adherence Questionnaire        | X                    |     | X | X  | X  | X      | X  | X            |             |
| Placenta/Cord Blood Collection |                      |     |   |    |    |        |    |              | X (Utah)    |

[figure not shown]

Modification to section D.11 on page 39: sub-study

The section name was:

**D.11 Sub-study**

It is changed to:

**D.11 Sub-studies**

The first paragraph is now a new sub-section D.11.a :

**D.11.a** "One sub-study will be conducted in the EAGeR trial to evaluate compliance...."

A new sub-section D.11.b. was added to describe the new GDM sub-study:

**D.11.b** Another sub-study will evaluate the role of adipocyte cytokines in the risk for gestational diabetes. This sub-study is titled: A study of novel adipocyte cytokines and the risk of gestational diabetes mellitus.

**Background:**

Gestational diabetes mellitus (GDM) is among the most common complications of pregnancy. Approximately 3-7% of all pregnancies are complicated by GDM, resulting in more than 200,000 cases annually (1). Importantly, this number is likely to increase as the prevalence of obesity among reproductive age women increases. Recent data have shown a substantial rise in the incidence of GDM from 1991 to 2000 (2) and a doubling from 1994 to 2002 (3). Women with GDM have increased risk for prenatal morbidity and a considerably elevated risk for impaired glucose tolerance and type 2 diabetes mellitus (type 2 DM) in the years following pregnancy. Children of women with GDM are more likely to be obese and have impaired glucose tolerance and diabetes in early adulthood. Although the precise underlying mechanism is yet to be identified, insulin resistance and inadequate insulin secretion to compensate for it play a central role in the pathophysiology of GDM. The metabolic challenges related to pregnancy reveal an otherwise undetected predisposition to glucose metabolic disorders in some women.

Excess adiposity is the single most important modifiable risk factor for the development of GDM. Mechanisms linking excess adiposity to elevated risk of GDM are not completely understood, but recent evidence points to a crucial role of specific hormones and cytokines ("adipokines") secreted by the adipose tissue. A major breakthrough in understanding the link between adiposity and glucose intolerance has come from the demonstration of a cross-talk between adipose tissue and other insulin target tissues such as skeletal muscle and liver. Such cross-talk is mediated by a number of molecules that are secreted by adipocytes and act in an autocrine, paracrine, or endocrine fashion. Among those identified to date are retinol binding protein 4 (RBP4), resistin, leptin, IL-6, and adiponectin (in particular, high molecular weight adiponectin). In concert, these cytokines, or 'adipokines', are believed to adapt metabolic fluxes to the amount of stored energy. Dysregulation of this network is believed to be a critical factor in the deterioration of insulin sensitivity that accompanies adiposity.

Despite the promising role of these novel adipocyte cytokines in the pathophysiology of insulin resistance, prospective studies of these adipokines in association with

[figure not shown]

GDM risk are sparse. The majority of limited available studies are small cross-sectional studies, inferences from which were hampered due to the ambiguous temporal relation between these adipokines and GDM risk. The major aim of this project is to prospectively investigate novel biochemical markers involved in adipokine secretion as predictors of GDM. In addition, we will examine whether these associations are independent of or modified by measures of overall and abdominal adiposity (BMI and waist circumference), and whether the associations between adipokines and GDM risk are mediated through elevated plasma free fatty acids.

Study design: A nested case-control study of 200 GDM cases and 400 controls based on longitudinal data from 2 prospective studies.

1. EAGeR Trial (PI [name]): In this study, 1600 women with a history of miscarriages will be recruited. Among them, approximately 960 women (60%) are expected to have successful pregnancy in 6 months of trying. Approximately 40-70 GDM cases are expected to result from this study. For these cases we will select 80-140 controls.

2. The National Standard for Normal Fetal Growth study (PI [name]): In this study, 2400 low risk women will be recruited. Among them, there would be 70-90 GDM cases. We will add an arm of 600 high risk pregnant women (being obese) to this study, among which there would be at least 60 GDM cases.

By combining these two studies, we expect to obtain 170-220 GDM cases. Longitudinal blood samples including before pregnancy (EAGeR trial), during the 1st, 2nd, and 3rd trimester and 6 weeks postpartum (Fetal Growth Study) will be collected.

Adding a blood collection in the 16th gestational week to the EAGeR trial will enable the investigation of changes in adipokine levels every four weeks before clinical GDM screening test (24-28 weeks), which is a crucial time window for studying the pathogenesis of GDM. The approximately 4 bio-specimens from each woman before GDM screening test will allow a greater precision in evaluating the longitudinal trend of adipokine levels and other important molecules within individual women. Moreover, the inclusion of 16 gestational week blood collection will enable the time windows for bio-specimen collection in the EAGeR trial to be comparable to those in the Fetal Growth Study, another data source for the 'Adipokines and GDM' project.

#### **Data collection and pregnancy follow-up**

The new "Week 16" visit will be identical to other pregnancy clinic visits with the same questionnaires administered and same blood and urine samples obtained. The consent for this sub-study is covered by the original consent.

## ***Effects of Aspirin in Gestation and Reproduction*** **The EAGeR Study**

Amendment to EAGeR Study Protocol, Version 2.3, March 17, 2008

### **AMENDMENT # 3, May 25, 2010**

#### **Protocol for Post – Withdrawal Telephone Interview**

We plan to contact EAGeR participants who withdraw from the study early to determine if they became pregnant after their withdrawal. This is participants who had no contact with study staff after their withdrawal. Participants will be contacted approximately 10-12 months after withdrawal. These contacts will be implemented in May 2010 and can begin once IRB approval is received. Those who withdrew more than 12 months before May 2010 will be contacted as soon as approval is received.

**Procedures:** Review each chart carefully before making any contacts with participants who withdrew from the study. If there are any concerns about contacting them, those concerns should be discussed with the PI or on a Conference Call with other EAGeR PIs and staff.

1. If a participant indicates “DO NOT CONTACT FOR ANY REASON,” do not contact.
2. If, in the assessment of the EAGeR team, it would cause undue stress to the participant, do not contact.
3. Place at least three telephone calls at different times of the day, for example, one in the morning, one in the afternoon and one in the evening. Telephone calls may also be attempted on weekends if time and resources allow it.
4. Initial contacts should be attempted by telephone. E-mail contacts are permitted if used while the participant was actively participating, but not as a first method of contact attempt.

The interview will be completed on paper, use the form **Post – Withdrawal Telephone Interview**.

# Chapter 1

## Interim Analysis

### 1.1 Preliminaries

#### 1.1.1 Sample size, proportions, and the test statistic

Let  $N = N_0 + N_1$  be the trial total sample size, where  $N_0$  is the sample size in the placebo group and  $N_1$  is the sample size in the treatment group. Let  $n_0, n_1$  be the number of completed participants at the time of the interim analysis, in the placebo and treatment groups respectively. Completed participant include all sort of completion except for withdrawal. In the following calculations we assume that  $n_0 = n_1$ , and define  $n = n_0 + n_1$ . In particular, we use the notation  $t = n/N$  in order to express the time  $t$ .

Let  $p_0$  be the proportion of live birth in the placebo group under  $H_0$ , and  $p_1$  be the proportion of live birth in the treatment group under  $H_1$ . Let  $\hat{p}_0(t)$ , and  $\hat{p}_1(t)$  be the observed proportions of live birth in the placebo and treatment groups at time  $t$  respectively. We denote the difference between the proportions by  $\delta = p_1 - p_0$ , and its estimator by  $\hat{\delta}(t) = \hat{p}_1(t) - \hat{p}_0(t)$ . Thus, if  $n_0 = n_1$ , we can use the identity  $t = n/N$ , and define the test statistic to be

$$Z(t) = \sqrt{t} \frac{\hat{\delta}(t) \sqrt{N}}{2\sigma}, \quad (1.1)$$

where

$$\sigma = \sqrt{\frac{p_1(1-p_1)}{2} + \frac{p_0(1-p_0)}{2}}. \quad (1.2)$$

Group sequential procedures for interim analysis are based on their equivalence to discrete boundary crossing of a Brownian motion process with drift parameter  $\theta$ . The test statistics  $Z(t)$  follow the multivariate normal distribution with means  $\sqrt{t}\theta$  and, for  $t_1 < t_2$ , covariances  $\sqrt{t_1/t_2}$ . The drift parameter  $\theta$  is related to the parameters of the z-test through the equation

$$\theta = \frac{\delta \sqrt{N}}{2\sigma}. \quad (1.3)$$

We note that  $\theta$  is independent of  $t$  and is pre-specified in the beginning of the trial.

In the sequel we consider the following scenarios. The total sample size is  $N = 1600$ , where  $N_1 = N_0 = 800$ . For the placebo proportion we consider the values  $p_0 = 0.4, 0.42, 0.44, 0.46, 0.48$ . The treatment proportions will be calculated as  $p_1 = RR * p_0$ , where  $RR$  is the relative risk according to the EAGeR protocol. Specifically, we consider  $RR = 1.15, 1.2, 1.25$ .

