#### **D.7b. Passive Follow-Up Phone Contacts**

The study staff will call participants at mid-cycle during passive follow-up. During these calls, following the script, the staff will administer the Safety Questionnaire and the Adherence Questionnaire. We will also reinforce the importance of adherence.

At the end of passive follow-up (end of 6th menstrual cycle), if no pregnancy is confirmed, subjects will be **closed** from regular participation in the study (no additional clinic visits), and the remaining medications will be collected. The non-pregnancy follow-up scheme is depicted in Figure 2.

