**Closeout of Pregnant Participants and Outcome Ascertainment:** Closeout will occur for all pregnant subjects within six to eight weeks of their final outcome (miscarriage, stillbirth, live birth, other). Any remaining study medications will be collected from the participants. A postpartum questionnaire will be conducted over the phone approximately six weeks after the participant's endpoint occurrence to obtain information about late complications for mother and child. Closeout will occur after the completion of the chart abstraction form for the course of pregnancy, delivery and late complications.

**Miscarriage:** For those experiencing SA information on dates, symptoms, procedures and location of visits to physician(s) will be asked. Where applicable, pathology records will be requested. A release(s) for records from their personal physician, any testing or treatment centers will also be secured to verify outcomes reported and dates. Information on support groups or counseling will be provided to these participants. The University of Utah will be taking bloods and performing karyotyping of the miscarriage tissues where tissue is available.

**Stillbirth:** For those with pregnancy loss after 20 weeks (stillbirth), information on dates, symptoms, procedures and location of visits to physician(s) will be asked. Where applicable, pathology records will be requested. A release(s) for records from their personal physician, any testing or treatment centers will also be secured to verify outcomes reported and dates. Complete information on the course of this pregnancy outcome will be abstracted from the physician and hospital records including information on both maternal and fetal complications. Information on support groups or counseling will be provided to these participants. The University of Utah will also be taking bloods when possible.

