### G2.2 Intention to treat analysis

The primary analysis of the clinical trial will be “intent to treat” (ITT) analysis based on the total cohort of randomized patients. This approach will be applied to the primary endpoint (live birth) as well as designated secondary endpoints. The difference between the incidence rates of live births for the two treatment groups will be examined by a two-sided test based on the standard Z-score (using the normal approximation to the binomial distribution). The common null hypothesis states that the effect of aspirin on the outcome is null compared to the placebo.

The secondary objectives (as described in Section A) with binary endpoints will be analyzed similarly as comparison of proportions. For binary outcomes such as pregnancy, the time to event may be of interest. In this case, survival analysis methods will be applied with the log-rank test for comparison of the two study treatment groups. For continuous outcome such as birthweight either parametric or non-parametric methods will be used as appropriate. If transformations to approximate a normal distribution are feasible, they will be carried out prior to the parametric analysis. The normality of the data will be examined both graphically using Q-Q plots and by formal tests (Wilks- Shapiro test). For data (either on original or transformed scale) assumed to be normally distributed the comparison of the two treatment groups will be carried out by a t-test. Alternatively if a non-parametric test is required, the Wilcoxon-Mann-Whitney test will be used.

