The following Tables 3 and 4 present results of power calculations for various interim looks plans for the EAGeR trial. These demonstrate the implications of different choices for the number and timing of interim looks. We assume throughout an alpha level of 0.05 and a sample size of 1600 women divided equally to the aspirin and placebo arms of the trial. Previously published studies suggest that for the control group a probability of about 0.70 - 0.80 for live birth given pregnancy ( $P_{preg}$ ) can be expected. Further, the probability of implantation per cycle ( $P_{implant}$ ) was assumed to be constant and in the range between 0.175 and 0.25. Figure 4 shows the probability of live birth (PLB) considering six cycles of menstruation (including both active and passive follow-up):

$$PLB = P_{preg} P_{implant} \sum_{c=1}^6 (1 - P_{implant})^{c-1}$$

**Figure 4.** Probability of live birth versus implantation probability per menstrual cycle

[figure not shown]

Hence a conservative estimate for the live birth rate would be a combination of implantation rate or 17.5% per cycle and a probability of live birth given pregnancy of 70% yielding an estimated value of  $PLB = 0.479$ . The final calculations will be done after the population from which participants are drawn will be identified. A refinement of the calculation can easily incorporate non-fixed probabilities of implantation per cycle

In the following, we consider a range of probabilities for the placebo + folic acid arm of 0.46, 0.48 and 0.50. The effect of the intervention will be measured as the rate ratio (RR) of live birth in the aspirin + folic acid arm compared to placebo + folic acid. We consider effect sizes of 1.15, 1.20 and 1.25. The calculations were preformed using PASS software. Table 3 presents the resulting power for no interim looks and Table 4 shows the power for one or two interim looks for selected outcome probabilities and effect size.

**Table 3.** Power for comparing live birth rates in treatment and placebo groups with no interim looks.

| Live Birth Probability in placebo arm | Live Birth Rate Ratio to be Detected |            |      |
|---------------------------------------|--------------------------------------|------------|------|
|                                       | 1.15                                 | 1.20       | 1.25 |
| 0.46                                  | .77                                  | .96        | .99  |

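### Interim live-birth rates are computed among completers, who over-represent failures during accrual, so the assumed mean of Z(t) does not hold at early looks

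*Supplement*

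**What the plan says.** Interim Analysis 1.1.1 defines n0 and n1 to "be the number of completed participants at the time of the interim analysis, in the placebo and treatment groups respectively", and adds: "Completed participant include all sort of completion except for withdrawal". It sets t = n/N and Z(t) = √t·δ̂(t)·√N/(2σ). Because √t·√N = √n, the observed proportions have completers as their denominator. The chapter states that Z(t) has mean √t·θ, with θ fixed at the start of the trial. The same statistic feeds the efficacy boundaries (1.1.2) and the conditional-power futility rule (1.1.3). Section 1.2 works through futility looks, including t = 0.2 and t = 0.3.

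The protocol sets when women complete:
- D.7b: at the end of the sixth cycle, "if no pregnancy is confirmed, subjects will be" closed.
- D.8: "Closeout will occur for all pregnant subjects within six to eight weeks of their final outcome".
- G.3: first births are expected about 10 months after randomization, and accrual runs through month 40.

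No section requires a minimum time since randomization before a woman enters the interim set.

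The final analysis differs. G2.2 specifies an "analysis based on the total cohort of randomized patients", using a "two-sided test based on the standard Z-score" for the difference in live-birth rates.

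**The concern.** When a woman completes depends on her outcome. Women who do not conceive, and women whose loss ends follow-up, complete months before women who give birth. While recruitment continues, a set chosen by completion therefore holds too many failures. The interim theory needs the opposite: the same expected rates at every t.

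Three things are at stake:
- The live-birth rates and the RR among completers do not estimate the final ones. G.3 names the RR as the measure of effect.
- The futility rule can stop an effective treatment more often than formula (1.10) says.
- Withdrawn women are excluded from the interim test but belong to the final intention-to-treat cohort, so the two tests concern different populations.

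**Working it through.** **Reproducing the plan.** G.3 gives "We assume throughout an alpha level of 0.05 and a sample size of 1600 women divided equally to the aspirin and placebo arms", and "implantation rate or 17.5% per cycle and a probability of live birth given pregnancy of 70" percent.
- Placebo live birth: conception within six cycles is 1 − 0.825⁶ = 0.6847, and 0.70 × 0.6847 = 0.4793 (stated 0.479).
- p0 = 0.48, p1 = 0.576: σ = √[(0.2496 + 0.2442)/2] = 0.4969, θ = 0.096 × 40/(2 × 0.4969) = 3.864, power Φ(3.864 − 1.96) = 0.97 (stated 97%).
- p0 = 0.40, p1 = 0.46: σ = 0.4942, θ = 2.43, power 0.68 (stated 68%).

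**Assumptions added here.** Accrual is even over 34 months (G.3, months 7–40) or 24 months (also implied in G.3). Cycles last 28 days with conception at mid-cycle. Birth comes 266 days after conception, and losses close about 45 days after conception. Closeout lag is 0 to about 7 weeks. hCG-detected losses that return to follow-up are not modelled. The aspirin effect acts through fewer losses (live birth given pregnancy 0.84) or more implantation (about 0.25 per cycle).

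**One case by hand** (34-month accrual, no lag, fewer losses, t = 0.45).
- Mean conception time is 2.26 months. Mean completion times are 10.99 months (birth), 3.73 (loss) and 5.52 (not pregnant).
- Mean over all outcomes, placebo: 0.4793 × 10.99 + 0.2054 × 3.73 + 0.3153 × 5.52 = 7.78. Aspirin: 0.5752 × 10.99 + 0.1096 × 3.73 + 0.3153 × 5.52 = 8.47.
- With even accrual, the number completed is proportional to T minus mean completion time. For t = 0.45, T = (7.78 + 8.47)/2 + 0.45 × 34 = 23.43 months.
- Placebo rate: 0.4793 × (23.43 − 10.99)/(23.43 − 7.78) = 0.381. Aspirin: 0.5752 × 12.43/14.95 = 0.478.
- RR = 1.26 against 1.20, and the difference is 0.097 against 0.096.

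**Across the assumptions** (true values 0.479, RR 1.20, difference 0.096; figures approximate):

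| t | placebo rate, completers | apparent RR | difference | E[Z] (planned) |
|---|---|---|---|---|
| 0.2 | 0.14–0.26 | 1.3–1.5 | 0.054–0.088 | 1.0–1.6 (1.73) |
| 0.3 | 0.24–0.34 | 1.3–1.4 | 0.08–0.095 | 1.7–2.1 (2.12) |
| 0.45 | 0.32–0.38 | 1.24–1.30 | 0.09–0.097 | 2.4–2.6 (2.59) |
| 0.6 | 0.36–0.41 | 1.23–1.27 | 0.09–0.098 | 2.9–3.05 (2.99) |

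**Futility in the chapter's low scenario** (p0 = 0.40, RR = 1.15, threshold 0.30).
- Planned, t = 0.45: b = −0.524 × √0.55 − 0.55 × 2.428 + 1.96 = 0.236, and Φ[(0.236 − 0.45 × 2.428)/√0.45] = 10.1%. The same formula gives 15.1% at t = 0.6.
- Among completers, take the lower p0 as a lower live-birth probability given pregnancy (0.40/0.6847 = 0.584). The hand case above then gives rates of 0.302 and 0.358, a difference of 0.055 instead of 0.060, and E[Z] = 0.055 × √720/(2 × 0.494) = 1.50 instead of 1.63. The SD of Z is 0.95. The boundary on the Z scale is 0.236/√0.45 = 0.351, so the stopping probability is Φ[(0.351 − 1.50)/0.95] = 11%.
- That is the mild end. Across the assumptions the range is about 11–15% at t = 0.45 and 16–20% at t = 0.6. At t = 0.2 it does not rise, because the smaller variance offsets the smaller mean.

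**Withdrawals.** Suppose 5% withdraw in one arm and 10% in the other (assumed), none with a live birth, with true rates equal at 0.48. Completer rates are 0.48/0.95 = 0.505 and 0.48/0.90 = 0.533, a spurious RR of 1.06.

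**The case against.** The strongest reply is that the decision statistic is the risk difference, not the RR. At the two looks that G.3 proposes (0.45 and 0.60), the difference is nearly unbiased when p0 = 0.48 and RR = 1.20. The chance of a false futility stop there is at most about 0.0025, against 0.0019 planned. G.3 adds that stopping will not rest on the tests alone, and the documents do not say which rates or ratios the DSMB will be shown. All this stands. It does not cover the looks at t = 0.2 and 0.3 that section 1.2 works through, nor the low-rate scenario.

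Two stronger readings are tempting but unsupported. A reader might infer that a low interim placebo rate would be used to reset the drift and so depress conditional power. Section 1.1.1 says θ is pre-specified, and 1.1.3 works with conditional power at that θ. The current-trend alternative it mentions is built from the difference. A reader might also infer that information time is overstated. Nothing computed shows this: at t = 0.45, E[Z] is close to plan, and the SD of Z under the null is below 1.

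Two further replies have some force. D.8 returns women with an hCG-detected loss to follow-up, and C.4 puts these at two thirds of losses. If all of those return (assumed), true placebo live birth becomes about 0.52 and completers at month 24 about 0.31–0.37. The size changes, but the downward bias remains. Also, the 1600 in G.1 already excludes dropouts, so t = n/N matches its own denominator. The mismatch is with the intention-to-treat cohort of the final test.

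**Conclusion.** The point holds. Selecting by completion makes the interim live-birth rates too low and, when aspirin works, the RR too high. It also makes the stated mean of Z(t) wrong during accrual. The bias in rates and RR is large at t = 0.2 and still material at t = 0.6. The effect on decisions is modest: an attenuated difference at t = 0.2–0.3, and a rise in false futility of roughly 1 to 5 percentage points at t = 0.45–0.6 in the p0 = 0.40, RR = 1.15 scenario.

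It should not be read as an inflated false-positive rate. With equal outcome timing and withdrawal in the arms, the null RR stays at 1.00 and type I error does not rise. The final analysis is untouched. The sizes rest on the assumed accrual, loss timing and closeout lag, and on leaving out hCG-loss returns. The direction of the bias in the rates was the same in every case tried. The definition should be changed before the first look.

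**What to change.** Base the interim test on all women randomized at least about 15 months before the data cut, analysed as randomized. Conception at mid-cycle six plus 266 days is 154 + 266 = 420 days, or 13.8 months, before any closeout lag. Seventeen months would cover births under 42-day cycles: 5 × 42 + 21 + 266 = 497 days, or 16.3 months.

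Keep withdrawn women in, counted by the same rule as in the final intention-to-treat analysis. One example is no live birth unless one is documented, with a completer sensitivity analysis. Define t as this cohort over the total number to be randomized, and state that total, since 1600 excludes dropouts. Report other completers descriptively, noting that their rates and RR do not estimate the final ones.

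Under the same assumptions, and with outcomes known for everyone in the cohort, expected rates return to 0.479 and 0.575, RR to 1.20 and E[Z] to √t·θ.

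The change needs one definition and one data filter. The cost is fewer women per look: about 29%, 40% and 58% of the total at months 30, 34 and 40, instead of about 46%, 58% and 75%. Equivalently, the same t comes about six months later. The t = 0.45 look moves from about 18.5–24.4 to 24.4–30.4 months after the first randomization.
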